##### Quality of life and self-care

Secondary measures include the 12-item Brunnsviken Brief Quality of Life (BBQ) questionnaire, which evaluates the importance and fulfillment of six areas (e.g., spare time, creative work, and friendship) [62]. Additionally, the 4-item Outcome Rating Scale (ORS) [63] will be used. Complementing these measures is the DAily Routines for Well-being INventory (DARWIN), developed by the research group (see Supplementary materials C), which evaluates the frequency of 11 behaviors relevant to mental health, including exercise, regular eating, socializing, and sleep hygiene.

##### Patient experiences, satisfaction, adverse events and treatment credibility

Patient experiences and perceptions will be measured using self-report forms, as well as further explored qualitatively during the FU12 interview. Subjective change in the patient’s condition since seeking care will be assessed using the one-item Patient Global Impression - Improvement (PGI-I) scale [64]. Satisfaction with care will be measured using a combination of four items [2, 5, 7, 8] from the Client Satisfaction Questionnaire (CSQ) [65], the Session Rating Scale (SRS) [66], and nine additional items tailored for Primary Care Behavioral Health (PCBH) settings to gauge patients’ perceptions and attitudes towards their care providers (see Supplementary materials C). The 5-item Treatment Credibility Scale evaluates how credible and effective participants perceive their treatment to be, enabling analyses of any link between perceived effectiveness and actual outcomes [67]. To evaluate treatment side effects, patients will complete an Adverse Events questionnaire, offered in both a concise (3 items) version at the FU4 and FU8 timepoints, and a more comprehensive version (9 items) at FU12, both available in Supplementary materials C. These allow patients to report and describe any unwanted treatment effects or events they may have experienced. Any adverse events requiring immediate action will be promptly reported to the responsible PCC.

#### Treatment content

Data on which interventions therapists use in each treatment modality will be extracted from medical records. Patients’ recollections of these interventions and which strategies they continue to use post-treatment will also be gathered qualitatively during the FU12 interview. Comparisons between treatment content in medical records, patient recollections and protocols (in GSH), as well as the broader evidence base (in BI), will be utilized to analyze variations in treatment outcomes. Medical records and interview responses will be coded using an inductive approach, where codes are developed directly from the data rather than from predefined categories. Double coding will be used to test inter-rater reliability, and any discrepancies will be resolved through discussion.

#### Feasibility, acceptability, and fidelity

##### Clinician experiences and preferences

Clinicians will be interviewed by a neutral research assistant to explore their perspectives on the extended assessment process, GSH, and BI. The interviews will examine their experiences, preferences, perceived differences between treatment approaches, and factors influencing treatment selection. Interviews will be transcribed and analyzed using thematic coding to identify key concepts, while each response is also rated on a numerical scale based on specific attributes (e.g., the usefulness, effectiveness, and adherence to each treatment model). Themes are developed inductively from the data, and coding is double-checked for inter-rater reliability. The interview guide is provided in the Supplementary Materials D.

##### Proportion of patients deemed suitable for GSH

The proportion of patients in the PCBH + GSH arm that are deemed suitable for GSH will be analyzed by both site and clinician. Potential sources of variation will be explored by examining patient characteristics, themes in clinician-reported reasons for not offering GSH to individual patients, and insights from clinician interviews. Retrospective assessments of suitability for structured interventions will also be conducted for patients who underwent extended assessments in practice, allowing for comparisons between the algorithm’s outcomes and real-life assessments.

##### Fidelity to GSH protocols and BI principles

Fidelity to each intervention will be assessed using data from medical records, the CRF, the FU12 interview, and free-form text responses from patient satisfaction and adverse event scales. To evaluate clinicians’ adherence to key treatment components, 5-point Likert scales will be used to interpret these data sources. For GSH, fidelity will be assessed based on factors such as the use of self-help materials, emphasis on core treatment components, alignment with the prescribed number of sessions, and consistency in treatment structure and focus. For BI treatments, key factors will include targeting changeable elements, maintaining focus, employing skill-building techniques, aligning with the evidence base, and ensuring clarity in treatment plans. These scales are provided in Supplementary Materials E, but may be somewhat adjusted prior to coding each treatment if the quality or content of the raw data differs from expectations. Fidelity will be analyzed both at the individual treatment level and averaged across clinicians and treatment models to assess overall adherence. To examine factors influencing variations in fidelity across sites, clinician interview responses will be analyzed as well as workload data. The Third Next Available Appointment (TNAA) metric, which measures the waiting time for a hypothetical patient seeking an appointment at the center, will serve as a proxy for clinician workload and will be used to assess whether higher workload correlates with lower fidelity to GSH protocols, or a reduced proportion of patients being deemed suitable for GSH.

#### Healthcare utilization and costs

The number of visits for each treatment type will be extracted from medical records. Treatment duration in hours will be calculated based on each site’s standard session length for in-person visits and phone or video consultations. Healthcare resource utilization and societal economic impact will be assessed using multiple measures. Direct treatment costs will be calculated based on the cost for self-help books, the number and duration of patient contacts, and the type of healthcare professional delivering the treatment. The Trimbos and iMTA questionnaire on Costs associated with Psychiatric Illness (TiC-P) will capture data on patient work productivity, including absenteeism due to sick leave, reduced efficiency while working, and productivity loss at home, as well as medication usage. The EQ-5D will be used to evaluate overall health-related quality of life for economic analyses.

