### Aim and purpose

The main purpose of the project is to evaluate if adding GSH as a treatment option within the PCBH framework (PCBH + GSH) – offered only to patients deemed suitable following a brief, structured assessment – can enhance treatment outcomes compared to the core PCBH model. Patient outcomes in the research questions below include everyday functioning (primary outcome) as well as disorder-specific symptoms. The research questions are as follows:

Primary question: When comparing patient outcomes at the care model level after 12 weeks, is PCBH + GSH more effective than the core PCBH model? If not, can non-inferiority of core PCBH be established?Among the subgroup of patients deemed suitable for structured interventions in both groups, do those receiving GSH in PCBH + GSH achieve better outcomes than those receiving BI in core PCBH? Additionally, is this effect more pronounced in patients with conditions expected to require specific treatment components, such as exposure therapy for anxiety disorders, compared to those with conditions like depression and stress, where the benefits of specific treatment components are less clearly established? If not, can non-inferiority of BI be established for these subgroups?Does adding GSH to PCBH increase treatment duration or costs of care delivery? Which model is more cost-effective, considering patient benefits in relation to healthcare and societal costs?Do the care models and treatments differ in patient satisfaction, adverse events, treatment content, and which behavioral changes patients make during and after treatment?Will the protocol-based intervention of GSH decrease variation in treatment outcome compared to BI, especially when comparing patients deemed suitable for structured interventions?In BI, do patients whose therapists use techniques aligned with evidence-based strategies for the patient’s specific symptoms (e.g., exposure for anxiety) achieve better outcomes? How do outcomes differ for various subgroups of patients receiving BI under different conditions, and how do these compare to the group receiving GSH? In GSH, how do therapists’ adherence to treatment protocols impact outcomes? More broadly, how does the specific treatment content, independent of which type of intervention it is provided in, influence patient outcomes?

Additionally, we want to explore if the PCBH + GSH model is feasible for large-scale implementation in healthcare.

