#### Guided self-help (GSH)

In this study, GSH is administered through self-help books tailored to specific disorders and supplemented with both individual 30-minute guiding sessions (conducted in-person or via video) and shorter 15-minute follow-ups (conducted over the phone or through brief video calls). Each GSH treatment contains between 3 and 6 contacts, of which a minimum of 1 and a maximum of 3 are longer guidance sessions. In contrast to BI practices, all guiding sessions are pre-planned at the outset of treatment. These are scheduled at key points in treatment, such as when the patient is starting exposure exercises in GSH targeting anxiety. The brief check-ins do not have to be pre-planned but can be incorporated as needed throughout the treatment, allowing for increased frequency for patients who require additional support. The role of the therapist is to motivate the patient to follow the program, especially during more demanding parts of the treatment, and to actively engage in practicing challenging exercises together with the patient. Each chapter of the books corresponds to the content of one session of face-to-face CBT, featuring psychoeducation, and practical exercises for documenting and challenging thoughts, emotions, and behavioral patterns contributing to the disorder. Typically, patients progress at a pace of one chapter per week, though this tempo can be adjusted based on individual needs.

GSH is offered using CBT self-help books for depression [32], generalized anxiety and worry [33, 34], illness anxiety disorder [35], social phobia [36], panic disorder [37], OCD [38], stress, adjustment disorder and exhaustion disorder [39], and insomnia [40]. All used books have been previously evaluated in research to ensure their efficacy and suitability, either in book format or text-based internet treatments [24, 32, 34, 41–46]. For depression and worry, the project has self-printed books based on internet treatments. For the depression book, some modifications were made to the original text, incorporating a stronger values-based component in behavioral activation, rather than focusing solely on increasing positive reinforcement [47]. The generalized anxiety and worry book underwent only minor changes to improve its appearance in print, with the content largely unchanged [34].

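### The rule for treatment hours assigns length by site and contact mode, so it cannot separate 30- from 15-minute guided self-help contacts held by video; hours and costs for research question 3 can be off in either direction

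*Protocol article*

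**What the plan says.** The section on healthcare utilization and costs sets the counting rule in two steps. For counts: "The number of visits for each treatment type will be extracted from medical records". For length, hours rest on each site's "standard session length for in-person visits and phone or video consultations". The result then enters the costing: "Direct treatment costs will be calculated based on the cost for self-help books, the number and duration of patient contacts", together with the type of professional.

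The section on guided self-help defines contacts differently. A course combines "individual 30-minute guiding sessions (conducted in-person or via video) and shorter 15-minute follow-ups (conducted over the phone or through brief video calls". The mix is also bounded: "Each GSH treatment contains between 3 and 6 contacts, of which a minimum of 1 and a maximum of 3 are longer guidance sessions".

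These hours serve research question 3 under Aim and purpose: "Does adding GSH to PCBH increase treatment duration or costs of care delivery". The same question asks which model is more cost-effective, and the data analysis plan answers that part with incremental cost-effectiveness ratios (ICERs).

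**The concern.** The utilization section ties length to site and mode. The GSH section ties it to the kind of contact, the same at every site. Video appears under both GSH contact types, and the utilization rule names phone and video together. Knowing that a contact was GSH and was by video therefore does not show whether 30 or 15 minutes were planned.

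The contrast in question 3 is between care models, and GSH exists in only one of them. An error specific to GSH contacts has no counterpart in the core arm to offset it. It passes into the difference in hours, then into direct cost and the numerator of the ICER. Multiple imputation and bootstrapping deal with missing values and sampling uncertainty; neither removes a systematic error in how minutes are assigned.

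**Working it through.** The protocol states no figure for treatment hours or cost, so there is none to reproduce. The check lists every permitted GSH course and compares its planned length with what the rule would assign.

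**Inputs from the protocol article**
- Guiding session 30 minutes, in person or by video; follow-up 15 minutes, by phone or brief video (GSH section).
- 3 to 6 contacts, of which 1 to 3 are guiding sessions (GSH section). This gives 12 mixes.
- Usual visit 30 minutes (Background, section on PCBH and brief interventions), taken here as the in-person standard.
- Extended assessment: two 30-minute visits (section on the extended diagnostic assessment).

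**Assumption.** The site's phone or video standard, L, is not given. L = 15, 20 and 30 minutes are tried.

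**Formulas**
- Planned minutes = 30 × guiding sessions + 15 × follow-ups.
- Error = (L − 30) × guiding sessions by video + (L − 15) × follow-ups. In-person guiding sessions at a 30-minute standard add nothing.

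**Case A: every GSH contact remote.** Selected mixes:

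| Guiding + follow-up | Planned min | Error, L = 15 | Error, L = 20 | Error, L = 30 |
|---|---|---|---|---|
| 1 + 2 | 60 | −15 | 0 | +30 |
| 3 + 0 | 90 | −45 | −30 | 0 |
| 2 + 2 | 90 | −30 | −10 | +30 |
| 1 + 5 | 105 | −15 | +15 | +75 |
| 2 + 4 | 120 | −30 | 0 | +60 |
| 3 + 3 | 135 | −45 | −15 | +45 |

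Over all 12 mixes:
- L = 15: −15 to −45 minutes, or −14% (−15/105) to −50% (−45/90).
- L = 20: −30 to +15 minutes. It cancels exactly for 1 + 2 and 2 + 4.
- L = 30: 0 to +75 minutes, or 0% to +71% (75/105).

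**Case B: guiding sessions in person at 30 minutes, follow-ups remote.** The error is (L − 15) × follow-ups:
- L = 15: 0.
- L = 20: 0 to +25 minutes.
- L = 30: 0 to +75 minutes.

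**Effect of the assessment visits.** The two visits add 60 minutes that the rule counts correctly at a 30-minute standard. For 3 + 3 the base becomes 195 minutes, so ±45 is ±23% instead of ±33%. For 1 + 5 it becomes 165 minutes, so +75 is +45% instead of +71%.

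**From patient to arm.** The mean error in the extended arm is the GSH share times the mean error per course. The share is not given. If it were 30% to 60% (an assumption), +45 minutes per course would be 0.30 × 45 = 13.5 to 0.60 × 45 = 27 minutes per extended-arm patient.

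**The case against.** The best defence is that mode follows length fairly well. Follow-ups are never in person and guiding sessions are never by phone, so splitting in-person from remote contacts largely reproduces 30 against 15 minutes. At a site with a 15-minute remote standard and in-person guiding sessions, the rule is exactly right. This stands, and it limits the claim. It does not remove the problem, because the protocol guarantees neither condition.

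A second defence is that visits are counted by treatment type and that a condensed article may leave unit lengths to a fuller plan, so GSH-specific lengths could still be used. The phrase on treatment type governs the count, though; the sentence on length names only the site standard. This is a stated rule that can give wrong hours, not an omitted detail.

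Third, 30 and 15 minutes are planned lengths, not observed time. The Discussion expects some sites to adjust duration or intensity under pressure. Brief interventions also include check-ins and are only typically given in 30-minute visits, so a site standard approximates those contacts too, in both arms. Giving GSH its planned minutes while brief interventions get site-standard minutes would bring in a difference in measurement by treatment. All of this stands and shapes the fix.

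A reader might infer that extended-arm hours and costs are definitely wrong, or that error is confined to that arm. The documents support neither. Site standards and video share are unknown, patients in the extended arm who receive brief interventions do not have this particular problem, and timing of brief interventions may carry error of its own.

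**Conclusion.** The two sections are not reconciled. As written, the rule cannot tell a 30-minute from a 15-minute GSH contact held by video, and it mis-times every follow-up at a site whose remote standard is not 15 minutes. Hours for GSH recipients can therefore be too low or too high, and direct costs and the ICER with them.

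The sign and size cannot be settled from the protocol. The widest figures, −45 to +75 minutes per course, need all-remote delivery for the undercount and a 30-minute remote standard for the overcount. Both are assumptions, and the percentages shrink once the assessment visits are included. No effect on the arm means or on the ICER is demonstrated, because the GSH share is also unknown.

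The rule should be corrected because question 3 rests on these hours and the correction is cheap. The question is secondary; the primary outcome and the sample size are untouched.

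**What to change.** When contacts are extracted from the medical records, code each GSH contact as guiding session or follow-up and assign its length by that type, not by mode. Use recorded or booked length in both arms wherever it is available. Where it is not, use the protocol-defined length for GSH contacts and the site standard for brief-intervention contacts. Feed the same hours into the duration comparison and the direct-cost calculation.

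Report a sensitivity analysis that applies the site-standard rule to all contacts in both arms. It shows how far the answer depends on the choice, and it guards against the fallback treating the two interventions differently.

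The cost is one more coding field during an extraction already planned, and slightly more time per GSH patient. Nothing in treatment delivery changes.

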### Automated algorithms

#### Automated assessment algorithm as a decision support tool

An automated algorithm will be used to assist clinicians in assessing the main problem area and determining suitability for GSH. In addition to the screening questionnaires outlined above, the algorithm utilizes vignettes featuring concise descriptions of each problem area targeted by GSH in the study (e.g., depression, worry/generalized anxiety disorder, social phobia, illness anxiety disorder, insomnia, stress and exhaustion disorder, panic disorder, and OCD), as well as two areas used to potentially disqualify patients from GSH treatment (life problems and distress due to medical conditions). These vignettes are available in Supplementary materials F. Patients are prompted to rate how accurately the description of each problem area reflects their problems (question A) on a scale from 0 to 4, where 0 represents “Not at all” and 4 represents “Completely”. They also rate the importance of each area and their motivation to address it (question B) on a scale from 1 to 4, where 1 represents “Not important at all” and 4 represents “Very important”. The rating for each vignette’s question A is multiplied by question B, generating a score between 0 and 16 for each problem area. After rating each problem area, patients select the one they consider most important to address, followed by their second priority. The algorithm then assigns 15 points to the top-rated problem area and 10 points to the second-most important one. Additionally, scoring above the cut-off on a given questionnaire (see Table 2), which indicates that a problem area may be significant and important to work with, adds 10 points for the respective problem area. Scoring below the cut-off yields 0 points. In this context, the cut-off does not indicate the likelihood of a diagnosis but rather whether the problem area is deemed to be relevant to the patient.

The automated algorithm calculates a total score between 0 and 51. A score of 51 can only be achieved if the same vignette is selected as both the most and second most important, which is permitted since it is possible for the patient to have one single, predominant issue. There is no formal cut-off score; however, a higher score indicates a greater likelihood that the patient is experiencing and willing to address a particular problem. Therefore, the results will not automatically determine the most suitable focus for the patient but serve as a decision-support tool for the clinician. High scores on the domains of life problems and distress due to medical conditions will be seen as indicators suggesting that GSH may not be the most suitable option, particularly if none of the GSH problem areas reach comparable levels. The algorithm does not incorporate the AUDIT-C and pain scores; instead, these scores are intended to be interpreted separately, alerting clinicians to potential issues that could diminish the suitability of GSH as a treatment option, even if one or more problem areas receive high points in the algorithm. Versions of this algorithm have previously been used in studies [68, 69].

#### Retrospective algorithm for assessing indication for structured treatment

To address research question (2) – which examines whether patients who would have been suitable for GSH but did not receive it face a risk of undertreatment – we have developed an assessment model to retrospectively evaluate patients’ indications for structured treatment related to mood disorders, anxiety, stress-related conditions, or insomnia among those randomized to the core PCBH model. The assessment model is designed to mirror the clinicians’ extended, diagnostic assessment as closely as possible, with the crucial distinction that categorization is based solely on self- and clinician-reported data, and patient treatment preferences are unknown since they are never offered the possibility to receive GSH. Patients in the core PCBH arm who are retrospectively assessed as not indicated for structured treatment are assigned to the CORE-N-BI group, while those who meet the criteria are placed in the CORE-I-BI group. The same retrospective assessment will be conducted for patients in the extended PCBH arm to allow for comparisons between the retrospective and real-life assessments; however, this will not impact their group assignment.

The retrospective assessment consists of four steps:

**Exclusion of patients clearly not indicated for structured treatment for the specified conditions**: These patients are identified based on their stated reasons for seeking help, reported health issues, and clinicians’ notes in the CRF.**Evaluation of potentially suitable patients**: Patients identified as potentially suitable for structured treatment undergo evaluation using specific scoring criteria, similar to those outlined in the decision support tool described above. In brief, this evaluation includes results from the automated algorithm, AUDIT-C scores, and the 1-item pain scale. Points are assigned when patients exhibit high scores in relevant problem areas, while deductions are made for high scores in non-relevant domains or indications of substance abuse or pain that may interfere with treatment.**Further evaluation of uncertain cases**: Patients with uncertain suitability are discussed with a supervisor and undergo additional evaluation, considering factors such as education level, health habits, and language difficulties.**Final assessment for suitable patients**: Patients deemed suitable for structured treatment have their primary problem areas assessed. The most pertinent problem is identified based on the problem area with the highest score from the automated algorithm, in conjunction with the patient’s stated reason for seeking help.

A flow chart detailing the process of the retrospective assessment can be found in Supplementary materials F.

